### Data collection and monitoring

Data will be directly inputted into a database created using the Research Electronic Data capture (REDCap) system and housed on the University of British Columbia REDCap server. All data inputted into REDCap will be site-specific and de-identified except for participant demographics such as year of birth and sex. Each site will maintain access to site-specific data through REDCap. Site coordinators will meet weekly to discuss study progress, trial deviations, and recruitment strategies. Any unfavourable or unintended symptoms or events (e.g., pain or soreness from intervention, falls) that occur to participants during the trial will be reported as an adverse event in REDCap. All minor adverse events will be reported to the data safety monitoring board (DSMB) every 4 months and will be classified on severity and potential relatedness to the trial. Instructors will modify or stop exercises if minor adverse events occur during exercise sessions. Serious adverse events will be reported directly to the DSMB within 48 hours and according to site-specific ethics protocols.

A fidelity check will be completed for assessments and exercise sessions by the central team (primary coordinator) at regular intervals to ensure the study protocols are followed consistently across sites. The fidelity check will focus on how session expectations are communicated to participants, how sessions are managed, how exercises are progressed, ensuring participant safety, and ensuring a supportive environment for participants is created. Feedback will be provided immediately to assessors and instructors if any deviations to the protocol occur.

### Sample size estimates

In individuals living with chronic stroke, the minimal detectable change in 30 s STS score ranges from 1.21 [36] to 3.23 repetitions [35] with the standard deviation ranging from 3.66 to 3.86 [35, 36]. Task-specific training has been shown to improve 30 s STS score in those with chronic stroke by an average of 2.1 repetitions post-intervention [48]. Thus, using STATA (StataCorp LLC, Version 14.2, USA), a sample of 86 participants are required to detect a minimal detectable change of 2.1 repetitions, with a standard deviation of 3.86, power of 0.80, significance of 0.05, and controlling for baseline correlations (0.45; based on data from Liu-Ambrose et al. [45]). Anticipating an approximate 15% dropout rate, we will recruit a total of 100 participants (50 per group).

### Data analyses

Descriptive statistics (mean and standard deviation, median and interquartile range for continuous variables, and frequency and percentages for categorical variables) will be used to summarize all demographic and outcome variables. Linear mixed models will be used to examine the relationship between group assignment in 30 s STS score (without the use of arms) controlling for baseline scores in the outcome. The independent variables included in all models will be group assignment, time point, and an interaction between group and time. This approach includes all participants with an observation at either baseline or 10 weeks post-intervention in the intention to treat analysis. A sensitivity analysis using multiple imputation to address any missing data will also be run.

Secondary outcomes will be analysed using linear mixed models to determine the relationships between group assignments, controlling for baseline scores in the outcome. As assessments and interventions will be delivered remotely and across geographical locations (with overlapping regions), site will not be a variable in the model.

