## Methods

### Study design

This study is an assessor-blinded, parallel-group, multi-site randomized controlled trial (Fig. 1). Participants will be randomized 1:1 to a 10-week Virtual Physical Activity Seated Exercise group (V-PASE) or a control group continuing with usual care (Control) after completion of the baseline assessment. The study will be delivered in real-time through videoconferencing services. Assessors will be blinded to the group assignments. The study protocol (Version 9, April 5th, 2024) is registered with clinicaltrials.gov (NCT05724823) and adheres to the Standard Protocol Items: Recommendations for Intervention Trials [24] and CONSORT [25] guidelines.

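### The mixed-model terms listed for the primary analysis do not give the baseline-adjusted T10 comparison on which the sample size of 86 rests

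*Protocol article*

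**What the plan says.** Assessments take place at T0 and T10 only (Outcomes, Table 1), and the primary endpoint is the modified 30 s sit-to-stand score at T10 (Primary outcome).

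The Sample size estimates section says that "a sample of 86 participants are required to detect a minimal detectable change of 2.1 repetitions". The other inputs are an SD of 3.86, 80% power and a 5% significance level. The calculation is also described as "controlling for baseline correlations (0.45", a value taken from another study. The section then allows for about 15% dropout and recruits 100, 50 per group.

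The Data analyses section uses linear mixed models for the primary and secondary outcomes and says, for both, that baseline values of the outcome are controlled for. It fixes the terms: "The independent variables included in all models will be group assignment, time point, and an interaction between group and time". It adds: "This approach includes all participants with an observation at either baseline or 10 weeks post-intervention in the intention to treat analysis". It names no coefficient or contrast as the primary test, no covariance structure and no constraint on the baseline means.

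**The concern.** With two assessment times, a time term and a group×time term can exist only if T0 is a response alongside T10. The inclusion rule confirms this, because a participant with a baseline value alone cannot contribute to a regression of T10 on baseline. Once a group main effect is also in the model, the baseline means are estimated separately by group. With complete data the interaction is then exactly the difference in mean change. That contrast has a different variance from the baseline-adjusted T10 difference.

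At stake is whether the primary analysis has the power stated for it. There is also a question of what controlling for baseline adds: if it means T0 enters as a covariate while it is already a response, the model's standard error may be wrong.

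**Working it through.** **Inputs.** Difference 2.1, SD 3.86, power 0.80, significance 0.05 and correlation rho = 0.45 come from Sample size estimates; 1:1 allocation comes from Study design. Sidedness is not stated. I take it as two-sided, which reproduces the plan's figure.

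**Formulas.** With variance factor f:
- n per arm = 2(1.96 + 0.8416)² × 3.86² × f / 2.1² = 53.04 × f
- SE = 3.86 × √(2f/n), and power = Φ(2.1/SE − 1.96)

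**Reproducing 86, then the alternatives**

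| Contrast | f at rho 0.45 | n per arm | Total | SE at 43 per arm | Power at 43 per arm |
|---|---|---|---|---|---|
| T10 adjusted for baseline (ANCOVA) | 1 − 0.45² = 0.7975 | 42.3 → 43 | 86 | 0.743 | 80.6% |
| T10 unadjusted | 1 | 53.0 → 54 | 108 | 0.832 | 71.3% |
| Difference in mean change (group×time) | 2(1 − 0.45) = 1.10 | 58.3 → 59 | 118 | 0.873 | 67.2% |

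Only the first row gives 86. The listed terms give the third row if the interaction is tested. They give the second row if the T10 difference is read from that model without a baseline covariate. Because rho is below 0.5, the change score is noisier than ignoring baseline.

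**Keeping baseline-only participants.** This recovers little. With 50 per arm at T0 and 42.5 at T10 (15% lost), the interaction variance is 2 × 3.86² × [(1 − rho)²/50 + (1 − rho²)/42.5] = 29.80 × (0.00605 + 0.01876) = 0.739. So SE = 0.860 and power is about 68.5%, against 66.7% for completers alone.

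**Dependence on rho (43 per arm)**

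| rho | ANCOVA power | Interaction power |
|---|---|---|
| 0.3 | 75.3% | 56.8% |
| 0.45 | 80.6% | 67.2% |
| 0.6 | 88.4% | 80.5% |
| 0.7 | 94.2% | 90.3% |

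**T0 as both response and covariate, with a random intercept.** In units of SD², the within-person mean square has expectation 1 − rho = 0.55. The between-person mean square, after regression on T0, has expectation (1 − rho²)/2 = 0.399. Because the second is smaller than the first, the random-intercept variance is estimated as zero and the two are pooled. The model variance is then too small by the factor (3 + rho)/4 = 0.8625, an SE ratio of 0.929 (0.81 reported against 0.87 true). The type I error of the interaction test is 2[1 − Φ(1.96 × 0.929)] = 6.9%. Simulation of 40,000 trials gave 7.0% to 7.2%, with the intercept variance at zero in more than 99.9% of them. Mixed-model fits to simulated data returned the same interaction estimate, the change-score difference, with and without the covariate. The ordinary change-score test held 5.1%.

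**The case against.** The strongest reply is that three statements point to a baseline-adjusted T10 difference: the endpoint definition, the sample-size basis, and the repeated remark about controlling for baseline. Only the list of terms points elsewhere, and an analysis plan not shown could settle the contrast and covariance. This stands as far as intent goes. It does not remove the conflict, because the article states its terms and inclusion rule, and these match neither ANCOVA (which has no time or group×time term) nor a constrained longitudinal model (which has no group main effect). An analysis plan would have to override them.

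A reader might infer that the trial simply has 67% power together with an inflated error rate. The documents do not support that. The 67% belongs to a valid 5% test of the interaction, and no primary contrast is named. The inflation belongs to a different model and needs T0 as a covariate plus a random-intercept structure, which the article never mentions. With an unstructured covariance or without the covariate, the interaction test holds about 5%. Double use of T0 also fits poorly with the inclusion rule, since a baseline covariate drops participants who have T10 only unless it is imputed.

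The 7% is also an upper-end figure at rho 0.45. Minimum Sufficient Balance allocation does not use baseline sit-to-stand, but it may reduce imbalance in it through correlated factors. If a share k of the chance imbalance variance remains, the true variance factor is 0.7975 + 0.3025k, against a model value of 1.10 × 0.8625 = 0.949. The error is then about 6.9% at k = 1, 5.9% at k = 0.75 and 5.0% at k = 0.5. The documents do not give k, so this range is an assumption.

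Finally, the correlation is borrowed from another study, and the power loss shrinks if the true value is higher. That is correct, but 0.45 is the plan's own value.

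**Conclusion.** Wrong as written. The stated terms conflict with the stated power, which is more than a detail left open. At the plan's own inputs and 43 per arm, the sized contrast has 80.6% power. The two valid contrasts that the listed terms offer have about 67% (group×time) and about 71% (T10 difference without a baseline covariate). The interaction recovers to about 81% only if rho is near 0.6. These figures assume a two-sided 5% test, equal SDs at T0 and T10, and the normal approximation.

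The type I error of up to about 7% is a separate, conditional point and should not be read as a property of the trial. Nor is there bias: under randomisation the interaction estimates the same treatment effect, and the cost is precision.

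**What to change.** For the primary and secondary outcomes, specify a constrained longitudinal model: T0 and T10 as responses, a common baseline mean with no group main effect, terms for time and for group at T10, an unstructured covariance, and no baseline covariate. Name the T10 group difference as the treatment effect. At the planning values this has the power the sample size assumes.

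ANCOVA of T10 on group and T0 also matches the sample-size calculation for participants with both values. It drops those without T10 unless they are imputed, so the constrained model fits the stated intention-to-treat inclusion rule better.

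If the unconstrained interaction is kept, restate the power as about 67%. Restoring 80% would need 118 evaluable participants, or 118/0.85 = 138.8, so 139 recruited.

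The preferred change costs wording only, with no new data and no more participants. Trial Status reports 57 randomised by 15 July 2025 and recruitment running to December 2026, so a dated amendment can still be made before the final analysis.

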### Study setting

The study will recruit community-dwelling people living with chronic stroke from sites in British Columbia, Saskatchewan, Manitoba, Ontario, and Nova Scotia that are associated with the Canstroke Recovery Trials Platform (https://canadianstroke.ca/). Recruitment will be conducted through affiliated hospitals and outpatient centres of site investigators and through local community and stroke recovery programs. The central research team at GF Strong Rehabilitation Centre (Vancouver, BC) will support individual sites on the study setup (including ethics), training, and processes. However, each site will independently recruit, consent, screen, enrol, schedule (assessments, exercise sessions, and blood work), input and manage data, and follow up participants. The central team will train staff at each site on the study protocols and will conduct fidelity assessments at regular intervals during the study.

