### Randomization

Randomization will be completed through an online third-party service (Diamind Solutions) following completion of the baseline assessment. Enrolled participants will be randomized within site, by coordinators, to the V-PASE or control group. Group allocation will be blinded for assessors only, and assessors will be instructed to refrain from asking the participant about study details. Randomization will be conducted using the Minimum Sufficient Balance (MSB) [26] algorithm that ensures balanced allocation across specific stratification factors. Participants will be stratified based on site, age (continuous variable; years), sex (categorical; male, female), time post-stroke (continuous; months), Modified Rankin Scale (continuous; 0–5), Fatigue Assessment Scale (continuous; 10–50), and walking speed calculated from the Timed Up and Go (continuous; cm/s).

The MSB algorithm will detect any imbalances in allocations across groups and will adjust the probability of assignment according to the following parameters. The first 10 participants will have a 50% (50/50) probability of being assigned to the V-PASE group or the control group. If an imbalance is detected in the next 80% of participants, the algorithm will adjust the probability assignment from 50/50 to 70/30. In the final 20% of participants, the probability will be adjusted to 90/10 to correct any imbalances.

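### Allocation is balanced on site and six baseline factors that the models leave out, so the analysis is conservative and inefficient if those factors predict the outcome beyond its baseline

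*Protocol article*

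**What the plan says.** The Randomization section uses a covariate-adaptive method: "Randomization will be conducted using the Minimum Sufficient Balance (MSB) [26] algorithm that ensures balanced allocation across specific stratification factors". The factors begin "Participants will be stratified based on site, age (continuous variable; years), sex (categorical; male, female), time post-stroke" and continue with Modified Rankin Scale, Fatigue Assessment Scale and walking speed from the Timed Up and Go (TUG). That makes site plus six baseline variables. After the first 10 participants, when an imbalance is detected, "the algorithm will adjust the probability assignment from 50/50 to 70/30", and to 90/10 in the final fifth. Allocation is local: "Enrolled participants will be randomized within site, by coordinators, to the V-PASE or control group". The Study setting section adds that "each site will independently recruit, consent, screen, enrol, schedule" and follow up their own participants, with central training and fidelity checks.

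The Data analyses section gives the terms of all models as group, time and their interaction, with control for the outcome's baseline score. None of the seven balancing factors is named as a term, and site is expressly excluded: "As assessments and interventions will be delivered remotely and across geographical locations (with overlapping regions), site will not be a variable in the model".

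The Sample size estimates section asks for 86 participants (2.1 repetitions, SD 3.86, power 0.80, significance 0.05, baseline correlation 0.45) and recruits 100.

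**The concern.** Forcing the arms to be alike on a prognostic factor removes that factor's contribution from the between-arm difference. A model without the factor leaves its variance in the residual, so the model-based standard error overstates the real uncertainty. The test then rejects less than 5% of the time under the null, and the intervals are wider than they need be.

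The reason given for dropping site does not answer this. Remote delivery and overlapping regions concern where participants live and how sessions reach them. Site in this design is the unit within which people are recruited, randomised, scheduled and followed, and videoconferencing does not change that.

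What is at stake is precision: data available on every participant before randomisation go unused in the analysis.

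**Working it through.** **1. The plan's own figure.** SD after baseline adjustment = 3.86 × √(1 − 0.45²) = 3.447. Per arm, n = 2 × (1.960 + 0.842)² × 3.447² / 2.1² = 42.3, so 43 per arm and 86 in total. The stated figure reproduces exactly (two-sided test). The sample size thus credits baseline Sit-To-Stand and nothing else.

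**2. Closed form for adjustment.** Let R² be the share of variance left after baseline Sit-To-Stand that the balancing factors explain. The documents do not give it, so a range is shown. With 43 per arm, SE = 3.447 × √(1 − R²) × √(2/43). This ignores the degrees of freedom spent.

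| R² | 95% CI half-width (repetitions) | Power | N for 80% power |
|---|---|---|---|
| 0 (as written) | 1.46 | 0.806 | 86 |
| 0.05 | 1.42 | 0.826 | 82 |
| 0.10 | 1.38 | 0.846 | 78 |
| 0.20 | 1.30 | 0.885 | 68 |
| 0.30 | 1.22 | 0.922 | 60 |

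Under perfect balance the unadjusted test has type I error 2 × [1 − Φ(1.96/√(1 − R²))], which is 2.8% at R² = 0.20.

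**3. Simulation of the allocation.** Balance is not perfect and covariates cost degrees of freedom, so the allocation was simulated twice, separately (A: 4,000 trials per scenario; B: 2,000). Inputs from the article: 100 randomised, 86 analysed, probabilities 50/50, 70/30 and 90/10. Assumptions: imbalance trigger p<0.3, five sites, and the R² values. A gives site 5% of the residual variance; B makes all factors equally prognostic. The analysis is ANCOVA on baseline Sit-To-Stand, with or without the six factors and site. Each cell shows A / B.

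| R² | Type I error, unadjusted | Type I error, adjusted | Power, unadjusted | Power, adjusted |
|---|---|---|---|---|
| 0 | 4.6% / 4.4% | 4.4% / 4.1% | 80.1% / 79.4% | 77.4% / 76.2% |
| 0.10 | 4.5% / 4.4% | 5.4% / 5.1% | 81.0% / 80.2% | 82.8% / 79.9% |
| 0.20 | 3.4% / 3.4% | 4.9% / 5.1% | 80.5% / 80.5% | 87.2% / 86.0% |
| 0.30 | 2.7% / 3.5% | 4.5% / 5.6% | 81.6% / 80.9% | 91.7% / 88.3% |

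Monte Carlo error in B is about 0.5 points on type I error and 0.9 on power. Mean CI width in B, unadjusted against adjusted: 2.98 against 3.08 at R² = 0; 2.97 against 2.92 at 0.10; 2.98 against 2.76 at 0.20; 2.98 against 2.58 at 0.30.

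**4. Does the gain carry over to the mixed model?** The article can be read as keeping baseline as a response and taking the effect from group × time. That contrast has SE of about 3.86 × √(2 × 0.55) × √(2/43) = 0.87. Covariates with the same effect at both times cancel from it. A check on 150 datasets (random-intercept model, simple 1:1 allocation rather than MSB) gave these mean model-based SEs:

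- Factors explain 20% of the variance at both times. Group × time: 0.862 without and 0.859 with the factors as main effects. ANCOVA: 0.754 and 0.759.
- Factors explain 20% of the 10-week variance left after baseline. Group × time: 0.863 without, 0.865 with main effects, 0.854 with covariate-by-time terms. ANCOVA: 0.747 and 0.716.

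So the gain appears only if the factors predict the 10-week score beyond baseline, and adding main effects to a group × time model would not deliver it.

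**The case against.** The strongest reply is that the harm is conditional and may be nil. The article already adjusts for baseline Sit-To-Stand, and nothing in it shows that walking speed, Rankin score or the other factors predict the 10-week score beyond that. At R² = 0.10 the gain is 0 to 2 points; at zero, adjusting costs about 3. This stands, and any statement of size must be conditional on it.

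A reader might infer that the trial falls short of its planned 80% power, or that its error rate is inflated. The documents support neither. The 86 rests on the baseline correlation alone, the unadjusted ANCOVA keeps 79–82% power in every scenario, and its type I error is at or below 5%. Any loss is relative to a more efficient analysis.

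The objection that main-effect covariates would not help a group × time contrast also stands, and it shapes the fix.

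Two further replies carry less weight. The authors do give a reason for omitting site, and central training and fidelity checks may reduce site differences; but neither undoes randomisation within sites that operate independently. And this is not a detail left to an analysis plan, since the article states the model terms and expressly excludes site. It is fair, though, that for the secondary TUG outcome the baseline score already carries the walking-speed factor.

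**Conclusion.** The mismatch between allocation and analysis is real and is stated in the text. Its direction is conservative. If the balancing factors explain 20% of the variance left after baseline Sit-To-Stand, the unadjusted test runs at about 3.4% type I error, with about 81% power against 86–87% adjusted. At 30% the gain is about 7 to 10 points; at 10% it is little or none; at 0% adjusting loses about 3 points. These figures rest on assumed R² values, an assumed trigger of p<0.3, five sites and an ANCOVA-type analysis.

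To say outright that the intervals are too wide and that power is lost would go beyond the documents, because they do not say how prognostic the factors are. This is an avoidable inefficiency with a weak justification for excluding site. It does not threaten the validity of the trial's conclusions.

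**What to change.** - Delete the sentence excluding site.
- In the primary model for 10-week Sit-To-Stand, pre-specify baseline Sit-To-Stand and the balancing factors as covariates (ANCOVA form): age, sex, months since stroke, Modified Rankin Scale, Fatigue Assessment Scale and baseline TUG walking speed. Enter site as a random intercept, or as a fixed effect with very small sites pooled by a pre-set rule.
- If baseline stays a response in the mixed model, enter the factors, including site, with covariate-by-time terms so that the 10-week contrast can benefit. The ANCOVA form gained more in the check above.
- Do the same for secondary outcomes, omitting baseline walking speed where the outcome is TUG.

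The cost is wording, about 10 degrees of freedom out of about 86 (six factors plus four site terms if there are five sites), and about 3 points of power if the factors are not prognostic. No new data are needed. The Trial Status section reports 57 randomised by July 2025, with recruitment expected to run to December 2026, so the change can be made before unblinding and will not look post hoc.
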